### Safety

All serious adverse events (SAE)/adverse events (AE) will be recorded on study specific adverse event forms. All AE’s will be registered with the local principle investigator (PI). These will be discussed at regular team meetings and collected and registered at the end of the study. All SAE’s will be registered centrally. In the case of an SAE, all site PI’s will be informed both at time of occurrence (with 24 h) and for a final conclusion on causality.

### Sample size

The sample size estimation was performed in “G*Power”, a statistical software program. The effect size was estimated, based on the effect size found in several studies examining the effect of exercise on cognition in elderly with MCI or increased risk for AD [8–10, 61, 62]. Sample size was calculated based on a two-tail statistical t-test set 1-β = 0.80, α = 0.05, an effect size of 0.4, an allocation ratio N2/N1 of 2. A total sample size of 224 was calculated. Considering a correlation of 0.5 between the outcome measures at T0 and T2, the design design-factor D = 1-0.52 = 0.75. The expected dropout rate is 25%. 224*0.75*1.25 = 210. Considering the fact that the primary analysis will be a combination of the results of three different centres, the final sample size *n* = 210 is rounded up to *n* = 225.

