### Statistical analysis

The primary analysis of this study will be comparison of cognitive functioning (primary outcome measure) between all three intervention arms before (T0) and after (T2) the 1 year intervention. A composite score will be calculated by averaging all six domain scores into one overall cognition score. The obtained scores per test will be converted into z-scores based on the standard deviation and mean of the total sample at baseline. In case of multiple tests within one domain, the average z-score for the domain will be calculated. Secondary outcome measures are the six separate cognitive domain scores and the other parameters.

For the primary analysis we will have an intervention group of *n* = 150 (both exercise forms together) and a control group of *n* = 75 as input of an ANCOVA with dependent variable the change in cognitive composite score between T2 and T0, and as covariates baseline cognitive functioning, sex, age. In a secondary analysis the comparison between the two exercise forms will be carried out in a similar ANCOVA analysis.

Analyses for all secondary outcome parameters will be carried out with similar ANCOVA analyses. Secondary analyses will also elucidate the contrasts between T0 and T1 and T2 for the primary and secondary outcomes, and thus elucidate the course over time, without correction for multiple comparisons, as these analyses are exploratory.

Furthermore, to assess change in physical fitness, quality of life, cerebral structure and epigenetics a similar statistical approach will be used as for the primary study parameter. A *p*-value of < 0.05 will be used to assess statistical significance.

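### Multiplying by 1.25 does not offset 25% dropout: the requirement is 224, not 210, and 14 of the 15 participants added for three centres are needed for dropout

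*Protocol article*

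**What the plan says.** The Sample size section of the protocol article builds the number in four steps.

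1. **Base number.** "Sample size was calculated based on a two-tail statistical t-test", with 80% power, a two-sided 5% level, "an effect size of 0.4" and "an allocation ratio N2/N1 of 2". The ratio matches the primary comparison in Statistical analysis, where 150 participants ("both exercise forms together") are set against 75 controls. The result: "A total sample size of 224 was calculated".
2. **Baseline adjustment.** "Considering a correlation of 0.5 between the outcome measures at T0 and T2", the number is multiplied by a design factor of 0.75. This is 1 − 0.5²; the superscript is lost in the text as read.
3. **Dropout.** "The expected dropout rate is 25%. 224*0.75*1.25 = 210".
4. **Round-up.** "Considering the fact that the primary analysis will be a combination of the results of three different centres", 210 is raised to 225.

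The abstract and the sections Study design, Recruitment and screening, and Statistical analysis all work with 225 in total or the 75s that make it up. The figure 210 appears only in the Sample size section.

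**The concern.** A dropout rate is a share of those randomised. To be left with a required number after losing a fraction d, one divides by (1 − d). Multiplying by (1 + d) gives a smaller number, and the gap widens as d grows. At 25% it is no longer a rounding matter.

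Two statements are affected. The section presents 210 as the number that already allows for 25% dropout, and it does not. It also assigns the step from 210 to 225 to the combination of three centres, so a reader would take 15 participants to be spare once dropout is covered. If dropout uses most of them, the plan has less reserve than it appears to have, and anyone judging the effect of slow recruitment or extra dropout starts from the wrong baseline.

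**Working it through.** **Inputs**, all from the Sample size section: standardised effect 0.4; two-sided level 0.05; power 0.80; allocation 2:1; T0–T2 correlation 0.5; dropout 25%.

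**Step 1: reproduce 224.** For a two-sample t-test the noncentrality is d × √(n₁n₂/(n₁+n₂)). With 75 and 149, 0.4 × √(75 × 149/224) = 2.83 on 222 degrees of freedom, and power is 80.3%. With 74 and 149 it is 79.97%. The stated 224 reproduces.

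**Step 2: number needed in the analysis.** 224 × (1 − 0.5²) = 224 × 0.75 = 168.

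**Step 3: reproduce 210.** 168 × 1.25 = 210. The printed figure comes from n × (1 + d).

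**Step 4: does 210 deliver 168 at 25% dropout?** 210 × 0.75 = 157.5, which is 10.5 short. The dropout that 210 does cover is 1 − 168/210 = 20%.

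**Step 5: correct inflation.** 168/(1 − 0.25) = 168/0.75 = 224. The shortfall is 224 − 210 = 14, or 14/210 = 6.7% of the stated figure.

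**Step 6: the planned 225.** 225 × 0.75 = 168.75 evaluable. The round-up adds 225 − 210 = 15 participants. Of these, 14 are needed to reach 224 and 225 − 224 = 1 is left. The dropout that 225 covers is 1 − 168/225 = 25.3%.

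**Step 7: power.** The design factor is equivalent to a standardised effect of 0.4/√0.75 = 0.462. With a 2:1 split of N evaluable participants the noncentrality is 0.462 × √(2N/9). Residual degrees of freedom are N − 5 (intercept, group, baseline score, sex and age, as in the planned ANCOVA).

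| Randomised | Evaluable at 25% dropout | Power |
|---|---|---|
| 210 | 157.5 | 77.5% |
| 224 | 168 | 80.1% |
| 225 | 168.75 | 80.3% |

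**The case against.** The strongest reply is that nothing in the trial changes. The target is 225 throughout, 225 exceeds 224, and power on the protocol's assumptions is still 80.3%. That stands in full. A reader might infer from the wrong figure that the trial is underpowered; the documents do not support this.

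A reader might also infer that the team could stop recruiting at 210. No section makes 210 a target or allows recruitment to end there; it is an intermediate step. Even at 210 the loss would be about 2.5 percentage points.

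A third tempting reading is that 225 is a sharp limit, so that any shortfall or any dropout above 25% takes power below 80%. This is not so: 224 randomised gives 80.1%, and 225 with 25.5% dropout still gives 80.03%. The margin is very thin, but it is not zero.

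The sentence about three centres is loose. It names no centre effect or inflation factor, and 225 also has the convenience of dividing into 25 per arm per site. Randomisation is of individuals, from a separate list for each country, and nothing in the document shows that a further allowance for centres is needed. So the point is not that a necessary allowance has been lost. It is that the reason given for the 15 is wrong, because dropout accounts for 14 of them.

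Finally, the section Withdrawal of participants says that those who withdraw will be invited to the T1 and T2 assessments, and that all randomised participants enter the primary analysis. Actual loss at T2 may therefore be below 25%, and 157.5 evaluable is the figure if every dropout is lost to the T2 analysis. This does not rescue the factor of 1.25: the calculation itself treats 25% as loss, and the inflation has to match the rate it states.

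**Conclusion.** The concern holds as a correction to one stated figure and its explanation. On the protocol's own inputs the number to randomise is 224, not 210. The stated 210 covers 20% dropout and would give about 77.5% power at 25%. The planned 225 remains adequate at about 80.3%, with one participant to spare out of the 15 that the section attributes to combining centres.

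These results take the effect size of 0.4, the correlation of 0.5 and the 25% dropout as given, and assume that dropouts provide no T2 score and are spread 2:1 across the two groups compared. No other section corrects the figure. The practical weight is limited, since neither the target, the design nor the primary analysis depends on 210.

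**What to change.** In the Sample size section:

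- Replace the calculation with 224 × 0.75/(1 − 0.25) = 224.
- State that 224 is rounded up to 225, which is 25 per arm per site (225/9).
- Remove 210 as a sufficient number, and remove the statement that the extra 15 reflect the three centres.
- Add that 225 leaves essentially no margin beyond the assumed 25% dropout. Do not present 225 or 25% as an exact threshold for 80% power.

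This rewrites a few sentences. The target, allocation and analysis stay as they are. The only cost is that the stated margin looks less favourable than before.

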### Statistical analysis

The primary analysis of this study will be comparison of cognitive functioning (primary outcome measure) between all three intervention arms before (T0) and after (T2) the 1 year intervention. A composite score will be calculated by averaging all six domain scores into one overall cognition score. The obtained scores per test will be converted into z-scores based on the standard deviation and mean of the total sample at baseline. In case of multiple tests within one domain, the average z-score for the domain will be calculated. Secondary outcome measures are the six separate cognitive domain scores and the other parameters.

For the primary analysis we will have an intervention group of *n* = 150 (both exercise forms together) and a control group of *n* = 75 as input of an ANCOVA with dependent variable the change in cognitive composite score between T2 and T0, and as covariates baseline cognitive functioning, sex, age. In a secondary analysis the comparison between the two exercise forms will be carried out in a similar ANCOVA analysis.

Analyses for all secondary outcome parameters will be carried out with similar ANCOVA analyses. Secondary analyses will also elucidate the contrasts between T0 and T1 and T2 for the primary and secondary outcomes, and thus elucidate the course over time, without correction for multiple comparisons, as these analyses are exploratory.

Furthermore, to assess change in physical fitness, quality of life, cerebral structure and epigenetics a similar statistical approach will be used as for the primary study parameter. A *p*-value of < 0.05 will be used to assess statistical significance.

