## Interventions

### Exercise intervention

The aim of both the aerobic intervention and stretching and toning exercise intervention groups will be to accrue 3 x 45 min exercise sessions per week over 12 months. Participants will complete a combination of supervised instructor led classes and unsupervised home exercise sessions. Class attendance and adherence to unsupervised home exercise sessions will be recorded for each participant by the class instructor each week over the 12 month intervention period.

The goal of the aerobic exercise class will be to accumulate at least 45 min of extensive aerobic exercise, prescribed by heart rate (HR) calculated as 180 bpm – age. Exercise intensity will be monitored during the supervised classes using a HR monitor and subjective reporting of the exercise intensity using the Borg’s Rating of Perceived Exertion (RPE) [36]. Participants in the aerobic exercise group will aim to achieve a target RPE of 13 while exercising. Each supervised class will be comprised of a 5–10 min warm up, 45 min of targeted aerobic exercise and a 5–10 min cool down. A range of aerobic exercise modalities will be offered including cycling, treadmill walking, elliptical training, endurance related indoor activities, outdoor walking, jogging and aqua jogging.

The aim of the stretching and toning group will be to complete non-aerobic activities. Each supervised class will be comprised of a 5–10 min warm up, 45 min of stretching, balance, coordination, relaxation, group games and light resistance exercises and a 5–10 min cool down. During the stretching and toning class, exercise intensity will not exceed an RPE of 10. Participants in the stretching and toning group will not be advised about aerobic activity and will not be instructed to avoid completing routine aerobic activity. The stretching and toning group will act as a social control group and it is not anticipated to see significant improvement in study outcomes.

The control group will receive usual care and will not be advised about exercise or attend supervised sessions. Participants in the control group will complete outcome assessments.

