## Discussion

To the best of our knowledge, there have been no intervention trials evaluating the effect of an extensive, controlled and structured 12-month exercise programme on the progression of cognitive decline in an MCI population. Since the neuropathological change process can take years after onset of MCI, the addition of longer intervention period may result in larger intervention effects. An important consideration of this study is the isolated aerobic exercise intervention. A number of exercise intervention studies have implemented multimodal exercise interventions [11, 63], making it difficult to interpret the effect of isolated exercise modalities. The large sample size, longer duration of exercise intervention, comprehensive neuropsychological test battery will enhance the existing research around exercise and cognitive function in MCI.

The secondary outcomes will examine several potential underlying mechanisms that may influence the exercise-cognitive relationship in MCI. The effect of exercise on brain structure and function measured by MRI brain will be examined. Methylation analyses of the APOE gene and neurotrophic genes will explore the effects of exercise on this known AD risk factor. Static gene polymorphisms will be used to predict intervention outcomes. Finally, cardiovascular fitness will be measured and examined as a moderator of the exercise-cognitive relationship in MCI. While cognitive performance is the primary outcome, we will also assess whether participation in a structured exercise programme or changes in cognition can influence quality of life and measures of frailty, known risk factors for cognitive further decline [64].

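### The pooled primary test is sized at d = 0.4 with no allowance for a weaker stretching arm, although the protocol does not anticipate significant improvement in that arm and expects aerobic exercise to do better

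*Protocol article*

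**What the plan says.** **Primary contrast.** The Statistical analysis section sets an exercise group of 150, described as "both exercise forms together) and a control group of" 75, in an ANCOVA of the T0 to T2 change in the cognitive composite. The covariates are baseline cognition, sex and age. Aerobic versus stretching is a secondary ANCOVA. No aerobic versus control contrast is named. The same section opens by calling the primary analysis a comparison "between all three intervention arms before (T0) and after (T2) the 1 year intervention".

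**Sample size.** The calculation is a "two-tail statistical t-test set 1-β = 0.80, α = 0.05", with "an effect size of 0.4, an allocation ratio N2/N1 of 2". It gives 224, multiplied by 0.75 for a T0–T2 correlation of 0.5 and by 1.25 for 25% dropout, which is 210, rounded up to 225. The effect size is "based on the effect size found in several studies examining the effect of exercise on cognition in elderly with MCI or increased risk for AD".

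**Role of the stretching arm.** The Exercise intervention section states: "The stretching and toning group will act as a social control group and it is not anticipated to see significant improvement in study outcomes". The Background says that the arm controls for the social side of a group programme, and reports mixed earlier results for such exercise.

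**Hypotheses.** The Study aims section places both exercise arms in the primary aim against control. Its secondary hypothesis is that aerobic exercise will have the stronger effect.

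**The concern.** A pooled contrast estimates the average of the effects in the two exercise arms. Setting that average at 0.4 is coherent if both arms are expected to reach about 0.4, or if aerobic exercise exceeds 0.4 by as much as stretching falls short. The protocol says neither. It describes half of the pooled group as a control for social contact, and it expects the two arms to differ.

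The stated 80% power may therefore not describe the trial that the protocol expects to run. A real aerobic benefit could be diluted and missed in the primary test, and a null pooled result would say little about aerobic exercise itself. The opening sentence of the Statistical analysis section adds a smaller problem: read literally, it describes a three-arm comparison, which is a different test from the pooled one.

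**Working it through.** **Inputs from the protocol.** Two-sided α = 0.05, power 0.80, d = 0.4, allocation 2:1, T0–T2 correlation r = 0.5, dropout 25%, and 75 randomised per arm.

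**Assumptions added here.** The aerobic effect is 0.4, dropout is equal across arms, and the SD is 1. The slight extra variance from mixing two unequal arms is ignored; it lowers power by less than one percentage point.

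**Step 1: the plan's own figure.** For a two-sample t-test the noncentrality is d × √(n₁n₂/(n₁+n₂)). With 75 and 149 (total 224) and d = 0.4 it is 2.825, and power is 80.3%. The 224 reproduces, and 224 × 0.75 × 1.25 = 210 also holds.

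**Step 2: the pooled effect.** With equal exercise arms, pooled d = (aerobic d + stretching d)/2. Adjustment for baseline rescales it to pooled d/√(1 − 0.5²) = pooled d/0.866.

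**Step 3: numbers analysed.** 75 × 0.75 = 56.25, so about 56 controls and 112 exercisers. √(56 × 112/168) = 6.110. For example, at pooled d = 0.30, noncentrality = 0.30/0.866 × 6.110 = 2.117.

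| Stretching d (aerobic 0.4) | Pooled d | Noncentrality, 56 vs 112 | Power, 56 vs 112 | Power if nobody drops out, 75 vs 150 |
|---|---|---|---|---|
| 0.4 | 0.40 | 2.822 | 80% | 90% |
| 0.3 | 0.35 | 2.469 | 69% | 81% |
| 0.2 | 0.30 | 2.117 | 56% | 68% |
| 0.1 | 0.25 | 1.764 | 42% | 53% |
| 0 | 0.20 | 1.411 | 29% | 37% |

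**Step 4: other ways to reach a mean of 0.4.** Aerobic 0.6 with stretching 0.2, or aerobic 0.8 with stretching 0, also gives a pooled d of 0.4 and 80% power. The protocol states no such aerobic effect.

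**Step 5: aerobic versus control, 56 vs 56.** √(56 × 56/112) = 5.292. At d = 0.4 the noncentrality is 0.4/0.866 × 5.292 = 2.444, and power is 68% whatever stretching does. Power reaches 80% near d = 0.47. The two contrasts have about equal power when pooled d = 0.4 × 5.292/6.110 = 0.346, which means stretching d = 2 × 0.346 − 0.4 = 0.29. Below that, aerobic versus control has more power; above it, the pooled contrast does.

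**Step 6: does the three-arm wording matter?** With 56 per arm and effects of 0.4, 0 and 0 (aerobic, stretching, control), a three-arm F test has 71% power, against 29% for the pooled contrast. The two tests are not interchangeable.

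**The case against.** **Pooling is the stated question.** The Study aims section defines the primary aim as both exercise forms against control, and the sample size and ANCOVA follow it. This stands. Pooling is a design choice, not a slip, and requiring aerobic versus control as primary would replace the trial's question. It would also leave the primary test at 68% power after the expected dropout. Reaching 80% at d = 0.4 takes about 75 completers per arm, so 75/0.75 = 100 randomised per arm, or 300 in all.

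**A reader might infer that the protocol expects a zero stretching effect, so that power is 29%.** The text does not support that. Not anticipating significant improvement is a statement about change within the arm. The primary hypothesis is about declining less than control, so a stretching arm that merely holds steady can still differ from a declining control. The Background also reports some earlier benefit from such exercise. The 29% is the bottom of a range.

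**A reader might infer that 80% power requires stretching to match aerobic exercise.** That follows only if 0.4 is the aerobic effect, which the Sample size section does not say. What is required is a mean of 0.4.

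**A reader might infer that the cited studies rule out 0.4 for the pooled group.** Those studies are not at hand, and the protocol does not say which of their comparisons produced the figure.

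**A reader might see the pooled test as repeating the fault that the Discussion finds in multimodal trials**, given its remark: "An important consideration of this study is the isolated aerobic exercise intervention". The parallel fails. Here the modalities are randomised separately and compared in a planned secondary analysis.

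**The three-arm sentence names no test.** This is fair. The only primary model specified is the pooled ANCOVA, so the sentence is loose wording, not a rival analysis.

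None of this removes the gap: the calculation allows nothing for a weaker stretching arm, although two other sections point to one.

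**Conclusion.** The point holds as an inconsistency between the power statement and the protocol's own description of the stretching arm. The arithmetic behind 224 is correct; the unstated assumption is a mean effect of 0.4 over both exercise arms. If aerobic exercise has d = 0.4, r = 0.5 and 25% of each arm drops out, power runs from 80% with equal effects, through 56% when stretching is half as effective, to 29% in the worst case of no stretching effect. With no dropout at all, 80% would still need stretching at about 0.29. If the aerobic effect is larger than 0.4, the shortfall is smaller and may vanish, but the protocol gives no figure to support that.

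**What to change.** 1. Reconcile the description of the stretching arm in the Exercise intervention section with the Study aims, Sample size and Statistical analysis sections.
2. If the pooled contrast stays primary, state in the Sample size section that d = 0.4 is the assumed mean effect of the two exercise arms, and add power for weaker stretching effects, such as the table above.
3. In the Statistical analysis section, replace the three-arm wording with the pooled contrast, so that one primary test is defined.
4. Fit the ANCOVA with arm as a three-level factor and name aerobic versus control as a key secondary contrast from the same model. State its power: about 68% at d = 0.4, and 80% near d = 0.47, after dropout.

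Making aerobic versus control primary is an option for the sponsor, not a required correction. It gains power if stretching is below about 0.29, loses some above that, and changes the primary hypothesis.

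The cost of items 1 to 4 is wording only, with no extra participants or data. The downside is that the stated power becomes less favourable.

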## Methods/design

### Study aims

The primary aim of this study is to investigate the effects a 12-month structured exercise programme (aerobic, and stretching and toning group) compared to a control group for the progression of cognitive decline in MCI. The primary hypothesis of this study is that participation in an extensive exercise programme will demonstrate a slower rate of cognitive decline compared to the control group. A secondary hypothesis is that participants in the aerobic exercise group will demonstrate a stronger positive effect of cognitive functioning than the stretching and toning (non-aerobic) group.

The secondary aims of this study are:To examine the effects of a structured exercise programme on MoCA scores, a screening tool of global cognition in MCITo determine the effects of a structured exercise programme on cardiovascular fitnessTo measure the effects of a structured exercise programme on physical activity levelsTo investigate a mechanism of action through epigenetic analysis and exploration of structural and functional changes on Magnetic Resonance Imaging (MRI) brain pre and post 12-month interventionTo investigate the effects of a structured exercise programme on quality of life measures and measures of frailty

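### The primary ANCOVA codes the two exercise arms as one group although they are expected to differ; a three-level arm factor with an equal-weight contrast tests the same hypothesis at almost no cost

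*Protocol article*

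**What the plan says.** The Statistical analysis section of the protocol article opens by describing the primary analysis as a comparison of all three arms. It then specifies a two-group model: an exercise group of 150 ("both exercise forms together) and a control group of" 75), with the T0-to-T2 change in the composite as outcome and baseline cognition, sex and age as covariates. No arm term within exercise is listed. The two programmes are compared elsewhere: "In a secondary analysis the comparison between the two exercise forms will be carried out in a similar ANCOVA analysis".

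The Sample size section matches the pooled question, with "two-tail statistical t-test set 1-β = 0.80", "an effect size of 0.4, an allocation ratio N2/N1 of 2" and a T0–T2 correlation of 0.5. On attrition it says "The expected dropout rate is 25"%, without a split by arm.

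Two other places bear on the coding. Under Study aims, the secondary hypothesis favours the aerobic arm: "participants in the aerobic exercise group will demonstrate a stronger positive effect of cognitive functioning than the stretching and toning (non-aerobic) group". Under Exercise intervention, the stretching arm is described as a social control in which no significant improvement is anticipated.

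**The concern.** Whether to pool is not in question: exercise against control is the stated primary hypothesis. The concern is how the pooled question is coded.

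A single exercise label treats the aerobic and stretching arms as having one common mean. If they differ, as the article hypothesises, the difference between them counts as random error and widens the standard error of the primary test. This happens even with perfect retention.

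The label also gives each exercise arm a weight equal to its share of the analysed exercise participants. With equal numbers that share is one half. If one arm supplied more month-12 values than the other, and the model used only observed changes, the quantity estimated would move towards the better-retained arm.

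**Working it through.** **The plan's own figure.** For a two-sided t-test with α = 0.05, d = 0.4 and 2:1 allocation, exact noncentral-t power is 0.8006 with 74 against 150 (total 224) and 0.7997 with 74 against 149. So 224 is reproduced, as is 224 × 0.75 × 1.25 = 210.

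**Inputs from the article.** Residual variance is 1 − 0.5² = 0.75 in squared SD units. There are 75 per arm and 25% dropout, hence 75 × 0.75 = 56.25 completers per arm (168.75 in all). The average exercise effect is 0.4 SD.

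**Inputs assumed here.** The separate effects A (aerobic) and S (stretching), and any dropout split between the two exercise arms, are not in the article.

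**Formulas**, with nA, nS and nC analysed and N = nA + nS + nC:

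- Pooled label, estimate: (nA·A + nS·S)/(nA + nS)
- Pooled label, residual variance: V = 0.75 + [nA·nS/(nA + nS)]·(A − S)²/N
- Pooled label, SE: √{V·[1/(nA + nS) + 1/nC]}
- Equal-weight contrast, estimate: (A + S)/2
- Equal-weight contrast, SE: √{0.75·[0.25/nA + 0.25/nS + 1/nC]}
- Power: noncentral t, with N − 5 degrees of freedom for the pooled model and N − 6 for the three-arm model.

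**Step 1: error term, equal retention (56.25 per arm).** Here nA·nS/(nA + nS) = 28.125. The contrast SE is √(0.75 × 0.02667) = 0.1414, with power 80.3%. Both methods estimate 0.400.

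- Effects 0.6/0.2: V = 0.75 + 28.125 × 0.16/168.75 = 0.7767 (+3.6%), SE 0.1439, power 78.9%.
- Effects 0.8/0: V = 0.75 + 28.125 × 0.64/168.75 = 0.8567 (+14.2%), SE 0.1511, power 74.9%.
- Effects 0.5/0.3: power 79.9%.

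**Step 2: weighting, only if month-12 values are missing unequally and observed changes are analysed.** Effects 0.6/0.2, control dropout 25%:

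| Dropout aerobic/stretching | Aerobic weight | Pooled estimate | Pooled power | Contrast estimate | Contrast power |
|---|---|---|---|---|---|
| 25%/25% | 0.500 | 0.400 | 78.9% | 0.400 | 80.3% |
| 30%/20% | 0.467 | 0.387 | 76.2% | 0.400 | 80.2% |
| 35%/15% | 0.433 | 0.373 | 73.2% | 0.400 | 80.0% |
| 20%/30% | 0.533 | 0.413 | 81.5% | 0.400 | 80.2% |
| 15%/35% | 0.567 | 0.427 | 83.8% | 0.400 | 80.0% |

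For example, at 35%/15% the weight is 48.75/112.5 = 0.433, and 0.433 × 0.6 + 0.567 × 0.2 = 0.373.

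**Step 3: cost when the arms do not differ (0.4/0.4).** With equal retention there is practically none. At 35%/15% the SE is 0.1418 against 0.1414 (+0.3%), and power is about 80.0% against 80.3%. A more extreme split costs more: with 40 and 70 exercise completers and 56 controls, the SE is 0.1441 against 0.1422.

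**Step 4: simulation.** In 8,000 simulated trials at 35%/15% with effects 0.6/0.2, the pooled label gave power 0.730 (mean estimate 0.375) and the contrast 0.799 (0.401). Under the null, rejection was 5.2% against 5.1%. In 6,000 trials with effects of +0.2 and −0.2 (average zero) and 47/65/56 completers, rejection was 5.4% against 5.3%.

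**The case against.** The strongest defence is that pooling two arms randomised 1:1 is a valid test of the stated primary hypothesis. On the article's own numbers (75 + 75) the pooled estimate equals the proposed contrast exactly. The section on withdrawal of participants puts all randomised participants in the primary analyses and invites those who withdraw to later assessments. The article states neither a completers-only analysis nor dropout by arm, and missing-data handling is commonly left to a fuller document. All of this stands.

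A reader might therefore infer too much: that the primary estimate will be weighted by who stays, or that the planned 80% power is lost. The documents do not support either. The drift needs four things together: missing month-12 values, analysis of observed changes, unequal retention and unequal arm effects. If the aerobic arm is the better retained, the pooled label has more power than the contrast (83.8% against 80.0% at 15%/35%), because its estimate then lies above the equal-weight effect. The difference in prescribed intensity between the programmes makes unequal retention possible but is no evidence for it or for its direction.

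The error-term effect survives the defence. It follows from the coding alone and needs only the arm difference that the article itself hypothesises. It is small: about 1.4 power points when the gap between arms is 0.4 SD, as large as the whole planned effect.

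**Conclusion.** The point holds as a minor, nearly free improvement. The two-group coding leaves any aerobic–stretching difference in the residual. At an average effect of 0.4 SD with equal retention, power falls from about 80% to about 79% (effects 0.6/0.2) or about 75% (0.8/0). The second case is the nearer to the description of stretching as a social control, but both pairs are assumptions, because the article gives no arm-specific effects.

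The drift of the estimate (0.373 to 0.427 across the splits shown) is conditional and can go either way. It is a reason to prefer fixed weights, not a demonstrated bias. Type I error is about 5% under both codings, so the planned test is not invalid.

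**What to change.** Fit one ANCOVA with arm as a three-level factor and the planned covariates. Define the primary test as the contrast 0.5 × (aerobic + stretching) − control, and take aerobic − stretching from the same model as the secondary test. This also reconciles the section's opening description of a three-arm comparison with the two-group model that follows.

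The cost is a change of wording and one degree of freedom. If the arms do not differ, the standard error rises by about 0.3% at 35%/15% dropout (0.2–0.3 power points), and by practically nothing with equal retention. No additional participants or data are needed. The change fixes the weights of the two programmes; it does not remove bias if those who drop out differ from those who stay.
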